#### Seizure monitoring

Seizure monitoring will be used to determine how treatment with the study compound affects seizure frequency duration. Caregivers will be asked to track the frequency and duration of their child’s three most frequent types of seizures on a daily basis using a study diary. In order for the study to remain consistent, the caregivers will track the same three types of seizures throughout the study. Seizures that occur in a cluster will be counted as one seizure although the duration of the cluster and number of seizures per cluster will be recorded. Although dialeptic seizures are not included as part of the inclusion criteria for the study, caregivers will be encouraged to record the frequency of dialeptic seizures if their child experienced them frequently.

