## Methods/Design

### Objectives

#### The primary objectives of the CARE-E study are:

To determine if a CBD-enriched *Cannabis* herbal extract is safe and well-tolerated for pediatric patients with treatment resistant epileptic encephalopathy.To monitor the effects of a CBD-enriched *Cannabis* herbal extract on the frequency and duration of specific seizure types.

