**Fig. 1 Fig1:**
[figure not shown]
A flow chart of participant enrollment, treatment with CBD-Enriched *Cannabis* herbal extract, monitoring and weaning

Recruitment Phase: Prospective participants will be directly identified and recruited through the caregivers by study physicians at each study site. Any potential participants’ caregiver will be contacted by the study physician or pediatric neurology nurse either in-person at the study physician’s clinic or by telephone. Prospective caregivers of participants will be asked if they are interested in having their child participate in the study. If the response is positive, a copy of the study brochure and consent form will be provided to them. Caregivers of prospective participants will be asked to attend a recruitment visit after they agree to participate in the study and provide informed consent. During the recruitment visit, the participant will be screened for eligibility based on specific inclusion and exclusion criteria. If the participant qualifies for the study, the participants’ caregivers will be instructed on use the study diary.

Inclusion and exclusion criteria: Participation in this study is inherent on meeting the following inclusion criteria: (1) Participants must be between the ages of 1 and 10 years of age with treatment-resistant epileptic encephalopathy including: Infantile Spasms, Continuous Spike Wave in Sleep, Lennox Gastaut, Doose, Landau-Kleffner and Dravet Syndromes and Malignant Migrating Partial Seizures of Infancy. ‘*Treatment-resistant’* will be in keeping with the International League Against Epilepsy (ILAE) definition of failing two appropriate anticonvulsant medications at therapeutic doses. (2) Participants must experience a minimum of at least one major seizure *per* week or four major seizures *per* month. For the purposes of this study, major seizures will be motor seizures including: atonic, tonic, clonic, tonic-clonic, major myoclonic, myoclonic astatic seizures and epileptic spasms. (3) Participants must be available to attend study assessments regularly and enter data into the seizure monitoring logs correctly. (4) Negative pregnancy test at screening for females who have reached menarche.

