Exclusion criteria for the study include (1) Recent (< 1 month) change in anticonvulsant therapies including anticonvulsant medications, ketogenic diet or settings on Vagal Nerve Stimulator (VNS) (2) Recent (< 6 months) change in intravenous immunoglobulin (IVIG) treatment. (3) Initiation of ketogenic diet within 6 months of study enrollment. (4) Implantation and activation of VNS within 12 months of study enrollment. (5) Use of cannabis-based therapy within two months of study enrollment. (6) Use of a Selective Serotonin Reuptake Inhibitor (SSRI), a tricyclic antidepressant, or an atypical neuroleptic in the month prior to study enrollment. (7) Concomitant regular concomitant use of narcotics (use of narcotics in emergency situations under the supervision of a physician is allowed). (8) Initiation or dosage change in oral or injectable steroid therapy within three months of study enrollment. (9) Allergy or known intolerance to any ingredient in the study compound. (10) Inability to attend assessments on a monthly basis. (11) Clinically significant cardiac, renal or hepatic disease (as assessed by the site investigator).

Subject Withdrawal Criteria: A participant may be withdrawn from the study if: (1) The study drug is causing intolerable side effects or a worsening in the participant’s seizures; (2) The caregiver fails to give the study drug to the participant as prescribed; (3) The caregiver does not bring the participant to appointments; (4) The study at a particular site is cancelled by the principal investigator, a site investigator or the institutional sponsor for administrative or other reasons. Whenever possible, the participant withdrawn from the study will continue to receive a dosage schedule that gradually weans the participant off the study drug over a one-month period. However, if the site investigator deems it medically necessary for the participants’ safety, the participant could be weaned off the study drug faster. All participants that complete the study will be asked to return for an end of study visit (Visit 7). All data collected about the participant during enrolment will be retained for analysis and the participant will not be replaced.

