Baseline Phase: Following the recruitment visit, participants will be sent home for one month with no change to their current anticonvulsant therapy, ketogenic diet, or Vagal Nerve Stimulator settings. Caregivers will be asked to track their child’s seizure frequency, duration, and use of rescue medication during this month. Rescue medications allowed for home-use include: Ativan (0.1–0.2 mg/kg PRN intrabucally, sublingual or IV), Midazolam (0.1–0.2 mg/kg PRN intranasally, intrabucally or IV), or Diazepam (0.2–0.5 mg/kg PRN rectally or IV). Other rescue medications may be administered by paramedics (under physician guidance) or physicians as *per* hospital guidelines or the child’s individual guidelines for management of *status epilepticus*. At the end of this month, participants and their caregivers will be required to visit the study clinic for a series of baseline tests including: blood and urine analyses, quality of life and cognitive/developmental assessments, neurological and general pediatric assessment, and an EEG lasting 2 h or until the participant falls asleep. Data from the seizure diaries will be collected and a new diary will be provided for the following month.

Treatment phase: Initiation of therapy: Following baseline testing, caregivers of participants will receive a 33-day supply of the 1:20 Δ^9^-THC:CBD *Cannabis* herbal extract from the site research pharmacist at visit 2. Caregivers of participants will be instructed to administer the study product at a 1:20 Δ^9^-THC:CBD *Cannabis* herbal extract dose of 2–3 mg/kg/day divided into two doses (BID). Caregivers will be further instructed to monitor their child’s seizure activity as defined above. In addition, they will be asked to monitor their child for any potential side effects such as drowsiness, ataxia, nausea, vomiting, worsening seizures, etc.

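### The diary follows three fixed seizure types chosen by frequency, not the major motor types that define eligibility, so a major motor type can be missing from the primary seizure data

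*Protocol article*

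**What the plan says.** All references are to the protocol article.

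- **Primary objectives.** The second is to monitor the extract's effects "on the frequency and duration of specific seizure types".
- **Inclusion criteria (under Study design).** A child needs at least one major seizure a week or four a month. The definition reads "For the purposes of this study, major seizures will be motor seizures including: atonic, tonic, clonic, tonic-clonic", and goes on to major myoclonic, myoclonic astatic seizures and epileptic spasms: seven motor types in all.
- **Seizure monitoring, types.** Caregivers record the child's "three most frequent types of seizures on a daily basis using a study diary". The choice is then frozen: "In order for the study to remain consistent, the caregivers will track the same three types of seizures throughout the study". Dialeptic seizures may be added if they are frequent; this is encouraged, not required.
- **Seizure monitoring, clusters.** "Seizures that occur in a cluster will be counted as one seizure", and the same sentence continues "although the duration of the cluster and number of seizures per cluster will be recorded".
- **Baseline phase.** Diary recording begins in the month after recruitment: "Following the recruitment visit, participants will be sent home for one month with no change to their current anticonvulsant therapy".
- **Safety route.** In the treatment phase caregivers also watch for worsening seizures as a possible side effect. The withdrawal criteria include the case where "The study drug is causing intolerable side effects or a worsening in the" participant's seizures.

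**The concern.** Children enter the study on one quantity, major motor seizures, and are followed on another, whichever three types occur most often. Nothing in the diary rule ensures that the two coincide. A child could qualify on four tonic-clonic seizures a month and have three other types that are more frequent; the qualifying type would then not be in the diary. A type that first appears on treatment has no place there either, because the list is fixed.

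This is a rule about what is collected, so it differs from a choice that the analysis plan can settle afterwards. A type without a baseline count and monthly counts cannot be analysed for change from baseline, or for the relation between dose and seizure frequency, which is a secondary objective.

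The cluster rule raises a second, smaller question. Epileptic spasms and Infantile Spasms are both included, and if such seizures come in clusters, a count of clusters need not follow the number of seizures.

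**Working it through.** The article gives no power, error rate or effect size for the seizure outcome, so there is no planned figure to reproduce. The check sets the rules side by side and then uses **assumed** counts to show what they do. None of the counts below comes from the article, except that 4 a month matches the eligibility minimum.

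**Step 1. Which seizures are in the diary?**

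| Case | In the three-type diary? | Other route |
|---|---|---|
| Major motor type among the three most frequent | Yes | – |
| Major motor type ranked fourth or lower | No | Side-effect report only |
| Type first seen on treatment | No | Side-effect report only |
| Frequent dialeptic seizures outside the three | Optional | – |

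No section adds a fourth type or an emerging type to the diary.

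**Step 2. Effect of an untracked type.** Let T be tracked seizures a month at baseline and u the untracked ones. Tracked seizures halve and the untracked type is multiplied by m. The diary shows -50% whatever u and m are. The all-type change is (0.5T + m·u)/(T + u) − 1.

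With u = 4 and m = 2:

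- T = 100: (50 + 8)/104 − 1 = -44%
- T = 40: (20 + 8)/44 − 1 = -36%
- T = 12: (6 + 8)/16 − 1 = -12.5%

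A further case: tracked types of 60, 30 and 20 (110 in total) fall to 55, and an untracked tonic-clonic type rises from 6 to 18. The diary shows 55/110 − 1 = -50%. All types give 73/116 − 1 = -37%. The rise of 18/6 − 1 = +200% in the untracked type appears nowhere in the diary.

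**Step 3. Effect of counting a cluster as one.** The counted change is the change in the number of clusters or isolated events. The individual change uses clusters × seizures per cluster.

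| Baseline | On treatment | Counted | Individual |
|---|---|---|---|
| 30 clusters of 10 (300) | 30 clusters of 5 (150) | 0% | -50% |
| 30 clusters of 10 (300) | 20 clusters of 15 (300) | -33% | 0% |
| 1 cluster of 30 (30) | 5 isolated (5) | +400% | -83% |

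The first and third rows understate a benefit and the second overstates one. The direction is not fixed.

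**Step 4. What can be recovered later?** The individual count can be rebuilt from the recorded number per cluster. Cluster duration is recorded too, and duration is part of the primary objective. The frequency and duration of an untracked type cannot be rebuilt from a diary that never held them.

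**The case against.** The case on the other side is substantial.

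- **Clusters.** The number per cluster and the cluster duration are kept, and the choice of count to analyse may be made in the statistical analysis plan, which is not shown. This stands. A reader might infer that within-cluster change is lost; the second half of the same sentence shows that it is not.
- **Safety.** Worsening seizures are watched for as a side effect at each dose and are a ground for withdrawal, in neither case limited to three types. Monthly neurological assessment, EEG and rescue-medication records add to this. A reader might infer that seizure aggravation would go undetected; the article does not support that. What remains is that a side-effect report gives no baseline count and no monthly rate for the untracked type.
- **Direction of bias.** A reader might infer that the rules favour the product overall. The cluster examples go both ways. An untracked type that worsens makes the diary look too favourable; one that improves more than the tracked types does the opposite. The article also defines no summed total and does not say exactly when the three types are chosen. Choice at or near the start is an inference from the fixed list and the baseline diary month. A claim that the choice itself produces an apparent fall is therefore not established.
- **Intended reading.** Dialeptic seizures are treated as an extra because they are outside the inclusion criteria, which hints that the three types were meant to be motor types. The rule does not say so, and even that reading leaves out a fourth motor type or a new one.
- **Scale.** This is a descriptive phase 1 study of 28 children, stated to be too small for definitive conclusions on efficacy. That lowers the weight of the point but does not remove it.

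**Conclusion.** The point holds in a limited form. The diary rule can leave a major motor seizure type out of the frequency and duration data for the second primary objective, in a child with more than three types or with a type that emerges on treatment. That loss is permanent, and no analysis plan can repair it. The number of children concerned is not stated, and the percentages above depend on assumed counts, so they show what can happen and not what is expected. Since the primary objective speaks of specific seizure types, restricting the types does not contradict it outright; the weakness is that they are selected by frequency instead of by the study's own definition of a major seizure.

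The cluster rule is a lesser matter. It can hide or distort change in the frequency count in either direction, and the recorded data allow this to be corrected.

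This should be fixed, because the remedy is cheap and the lost data cannot be regained. It does not invalidate a descriptive phase 1 study whose safety objective has its own reporting route.

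**What to change.** Reword the Seizure monitoring section on three points.

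1. The diary records every major motor seizure type listed in the inclusion criteria, plus any type first seen after entry, with the date on which it first appeared.
2. The three most frequent types are kept as a descriptive breakdown and no longer set the limit of what is recorded.
3. Frequency is reported by individual seizures, using the recorded number per cluster, alongside the count that treats a cluster as one.

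The cost is a revised diary page and a short change of text. Caregivers of children with more than three types, or with a new type, would have slightly more to record; the number per cluster is already collected.

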#### Use of rescue medication

Caregivers will be asked to track their child’s use of rescue medication. This will determine whether treatment with the study compound has any influence on use of rescue medication. Caregivers will record the medication used, the dosage used, and the number of times it was administered.

### Sample size determination

As CARE-E is a phase I dose escalation safety and tolerability study designed to find the most appropriate dose of CBD in a pediatric population it was felt that power analysis was not required to calculate sample size. The sample size of 28 participants each receiving 4 separate dosage escalations is within usual guidelines for standard phase I clinical trial designs. In this multi-site dose escalation study, we chose to escalate within the same participant with 7 participants at each site because the low pediatric population incidence of epileptic encephalopathy (the inclusion criterion), precluded ability to escalate in cohorts of 6, where a new cohort of six would be administered the next dosing level [20, 21]. Any patient exhibiting a dose limiting toxicity will not receive the next dose escalation.

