Monthly follow-up: Caregivers will return to the clinic for the monthly testing as described above. Data from the study diaries will be copied for analysis. Following the completion of testing, parents will receive a new 33-day supply of the 1:20 THC:CBD *Cannabis* herbal extract from the research pharmacist. Parents will be instructed to administer the extract at increasing doses over the next 3 months; i.e. at 5–6 mg/kg/day divided BID at visit 3, 8–10 mg/kg/day divided BID at visit 4, and 10–12 mg/kg/day divided BID at visit 5. If the participant experiences significant side-effects at a certain dose, the subsequent CBD dose will be adjusted to the mid-point between their current dose and former dose. Parents will be instructed to continue tracking their child’s seizure activity and monitoring the child for potential side effects in the same manner as the initiation of therapy month.

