#### Regarding calculation of dosage and distribution of 1:20 Δ^9^-THC:CBD Cannabis herbal extract at each study visit

To ensure consistency between centers in the dosing regimen for their study participants, for each dosing increment for the participant, the mid-point value of the dosage range be chosen and the daily dosage be rounded to the nearest 10 mg CBD (0.5 ml of *Cannabis* Extract). This will also allow for greater ease and accuracy in administering the study drug to the participants by their caregivers. For example, a participant who weighs 25 kg at Visit 1 would be prescribed a daily dose of 60 mg CBD (2.4 mg/kg/day) to commence on Visit 2. The dosage for each visit would be calculated on the preceding visit to allow time for the site’s research pharmacy to order the study drug so it can be delivered on time by the producer.

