Weaning phase: Termination of treatment: At visit 6 (after completing 1 month of CBD at 10–12 mg/kg/day) participants will return to the clinic for a final series of tests which include: blood and urine analyses, quality of life and cognitive/developmental assessments, neurological and general pediatric assessments, and EEG. Participants will be provided with a one-month weaning schedule which incrementally decreases the dose of the 1:20 Δ^9^-THC:CBD *Cannabis* herbal extract administered (CBD at 8–9 mg/kg/day for 1 week then 5–6 mg/kg/day for 1 week then 2–3 mg/kg/day for 1 week prior to discontinuing the study product).

Final Assessment: Participants will return to the clinic upon completion of the one-month weaning period. Caregivers will provide observations of any side-effects noted during the weaning period and will complete a final quality of life questionnaire. Data from the seizure monitoring diaries will be collected and caregivers will be asked to return any leftover study drug.

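### The weaning schedule is written in fixed doses for children who reached the top level; applied as stated, its first step raises the dose for some children held back for toxicity

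*Protocol article*

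**What the plan says.** All references are to the protocol article.

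**Escalation.** Caregivers start at 2–3 mg/kg/day of CBD at visit 2 (Treatment phase: Initiation of therapy). Later levels are set "at 5–6 mg/kg/day divided BID at visit 3, 8–10 mg/kg/day divided BID at visit 4, and 10–12 mg/kg/day divided BID at visit 5" (Monthly follow-up). For uniform dosing across centres, "the mid-point value of the dosage range be chosen and the daily dosage be rounded to the nearest 10 mg CBD" (Regarding calculation of dosage and distribution).

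**Toxicity.** Three places say what may happen:
- Monthly follow-up: after significant side-effects, "the subsequent CBD dose will be adjusted to the mid-point between their current dose and former dose".
- Sample size determination: "Any patient exhibiting a dose limiting toxicity will not receive the next dose escalation".
- Subject Withdrawal Criteria: a child may be withdrawn if "The study drug is causing intolerable side effects or a worsening in the participant’s seizures". A withdrawn child is to be weaned gradually over a month where possible, or faster if medically necessary. No doses are given.

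**Weaning.** The section Weaning phase: Termination of treatment describes visit 6 as following a month at 10–12 mg/kg/day. It continues: "Participants will be provided with a one-month weaning schedule which incrementally decreases the dose of the" extract. The steps are 8–9, 5–6 and 2–3 mg/kg/day, one week each. No version is given for a child who is below the top level at visit 6.

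**The concern.** The weaning steps are absolute doses, not fractions of the dose the child is on. They step down only if the child starts above the first of them. The toxicity rules produce children who do not. For some of these children the stated first step is a rise, and they are the ones who were held or reduced because they tolerated the product poorly. Dosing is done at home by caregivers, so the written schedule matters.

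There is also a consequence for the analysis. The article says the trial is designed to find the most appropriate dose, and its secondary objectives relate dose escalation to adverse effects and to trough cannabinoid levels. After a toxicity, two children at the same visit can be on different doses. Summaries that take dose from the visit number would put adverse events and trough levels under a dose that the child was not receiving, both in the later treatment months and during weaning.

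**Working it through.** **Check of the dosing convention.** The article's example is a 25 kg child at the first level. Mid-point of 2–3 is 2.5; 2.5 × 25 = 62.5 mg/day; rounded to the nearest 10 mg this is 60 mg/day; 60 / 25 = 2.4 mg/kg/day. This matches the article, so mid-points are the right basis for what follows.

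**Inputs (mg/kg/day).**
- Level mid-points: 2.5, 5.5, 9 and 11.
- First weaning step: 8–9, mid-point (8 + 9) / 2 = 8.5. The article does not say expressly that the mid-point convention covers weaning, so the range is shown as well.

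**Doses below the top level.**
- No further escalation: 2.5, 5.5 or 9. The article names no continuing dose; staying at the current level is an assumption.
- Mid-point reduction: from 5.5, (5.5 + 2.5) / 2 = 4.0; from 9, (9 + 5.5) / 2 = 7.25; from 11, (11 + 9) / 2 = 10.

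**First weaning step divided by current dose.**

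| Dose at visit 6 | How reached | 8.5 / dose | 8 / dose to 9 / dose |
|---|---|---|---|
| 2.5 | held at level 1 | 3.40 | 3.20 to 3.60 |
| 4.0 | reduced from 5.5 | 2.13 | 2.00 to 2.25 |
| 5.5 | held at level 2 | 1.55 | 1.45 to 1.64 |
| 7.25 | reduced from 9 | 1.17 | 1.10 to 1.24 |
| 9 | held at level 3 | 0.94 | 0.89 to 1.00 |
| 10 | reduced from 11 | 0.85 | 0.80 to 0.90 |
| 11 | full escalation | 0.77 | 0.73 to 0.82 |

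The first four rows are increases across the whole 8–9 range. The last three are not. For a 25 kg child held at 5.5, the step is from 5.5 × 25 = 137.5 to 8.5 × 25 = 212.5 mg/day before rounding.

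**How firm each row is.** The 7.25 row follows most directly. Side-effects in the third treatment month (9 mg/kg/day) put the fourth month at 7.25, and visit 6 comes next. The rows at 2.5, 4.0 and 5.5 also assume that the child does not escalate again before visit 6, which the article neither allows nor rules out. A child reduced at the first level has no former dose, so no figure is relied on there.

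**The toxicity rules side by side.** A child with toxicity at 5.5 goes to 4.0 if the event counts as a significant side-effect. If it counts as a dose limiting toxicity, the child does not go to 9. If it counts as intolerable, the child may be withdrawn. Moving to 4.0 also satisfies the no-escalation rule, so the first two can be obeyed together. They still permit different doses at the same visit.

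**The case against.** The best defence is that the weaning paragraph, on its own terms, covers only children who completed a month at 10–12 mg/kg/day. It says that the dose goes down, and no sentence directs a child on 5.5 to take 8–9. A sensible site would follow the stated intent rather than the figures. This has force: the increase is conditional on the figures being applied. It does not remove the problem. The paragraph refers to participants without exception, the article's own rules create children outside its premise, and the withdrawal text gives no doses to use instead.

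A reader might infer more than the article supports:
- **That the toxicity rules contradict each other.** They do not strictly. A reduction is also a non-escalation, and withdrawal is discretionary. The three differently named triggers may be graded responses, and their definitions may stand in the full protocol, which is not shown.
- **That every child held back would get a higher dose.** At mid-points, a child on 9 or 10 would not.
- **That three weekly steps cannot make a one-month wean, or that 8–9 is wrong because the escalation level is 8–10.** Neither is shown to be an error. The remaining days may be drug-free before the final visit, and a taper step need not equal an escalation level.

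It is also fair that dispensed and returned amounts are logged and checked against each child's daily dose, and that analysis detail is deferred to the analysis plan. So the dose given may well be recoverable. The point is that it has to be used.

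**Conclusion.** The point stands in limited form. The only weaning schedule with stated doses presumes the top level, while two rules elsewhere in the article leave some children below it. Applied as written, the first step is an increase of about 1.2 to 3.4 times for a child on 7.25, 5.5, 4.0 or 2.5 mg/kg/day, against the schedule's stated purpose. It is not an increase at mid-points for a child on 9 or 10.

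This rests on mid-point dosing, on the stated figures being used literally and, for doses of 5.5 and below, on the child remaining at that dose until visit 6. How many of the 28 children would be affected cannot be derived, because the article gives no expected toxicity rate.

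The different actions attached to overlapping triggers do not amount to a strict contradiction. They do mean that visit number is not a reliable stand-in for dose after toxicity. The sample size is not affected; it rests on no power calculation.

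**What to change.** Reconcile the weaning text with Subject Withdrawal Criteria, Monthly follow-up and Sample size determination, so that it agrees with its own stated intent for children who did not reach 10–12 mg/kg/day. In the same pass, make clear how the toxicity rules relate to one another and whether a child who was held or reduced may escalate later. Which rule and which doses apply is for the clinical team; none is proposed here.

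For the analysis, relate adverse events, tolerability and trough levels to the dose actually given at the time, not to the dose that the visit number implies. The dispensing and return logs already described should supply much of this; if daily dose is not already on the case report form, add it.

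The cost is a short amendment and, at most, one data field. The amendment should be in place before any child below the top level reaches visit 6.
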